**Fig. 3 Fig3:**
[figure not shown]
SPIRIT figure for SafeCare+ trial for data collection timings

### Data analyses

#### Quantitative analyses

Primary analyses will be based on generalized linear mixed models [38–40]. Mixed models are necessary for analyzing data from the proposed project because the data will have a three-level, hierarchical data structure in which measurements over time are nested within clients and clients are nested within provider. The models tested involve both fixed and time-varying covariates. All models will be multivariate in nature (i.e., testing all predictors simultaneously). Significance tests will focus on individual regression coefficients from the models. In addition, the final data set will offer rich opportunities for auxiliary or secondary analyses, including exploring the role of fidelity for mediating client outcomes. Dependent variables will be changed in (1) reports of DV on the CTS, (2) depression, (3) relationship self-efficacy, and (4) indicators of fidelity to SC and SC+.

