#### Outcome measures

*SC+ model fidelity* is assessed via client report, with clients completing a fidelity questionnaire at the end of every SC or SC+ session. The fidelity survey was adapted from the National SafeCare Training and Research Center training checklists, and the fidelity measure has been validated over the course of SC implementation [31]. Overall, monitoring of fidelity allows for measuring the effectiveness of the intervention as designed, as well as any practice changes which are naturally occurring and may need to be addressed.

*The Conflict Tactics Scales* (CTS2)*-short form* [32, 33] measures both the extent to which partners in a dating, cohabiting, or marital relationship engage in psychological and physical attacks on each other, as well as use of reasoning or negotiation to deal with conflicts. Participants are asked about the frequency of concrete acts and events within the past 6 months for their baseline CTS2 assessment, with the time frame changed to assessing if these acts and events occur within the past 2 months for the post-intervention assessment.

*The Center for Epidemiological Studies Depression Scale* (CES-D) [34] is a 20-item questionnaire, which assesses depressive symptomology. Designed as a short self-report tool, each item asks about the last week and is responded to using a 4-point format. The CES-D has high internal consistency and adequate test-retest repeatability.

*Relationship self-efficacy* (RSE) [35] is a 35-item measure evaluating relationship maintenance self-efficacy beliefs. Thirteen items relevant to the content of HR are included, across the three domains of emotional control, differentiation, and mutuality. Emotional control denotes the ability to appropriately regulate negative feelings with others. Differentiation is the capacity to assert clear interpersonal boundaries and express the need for separateness. Mutuality is defined as being able to provide care and receive support.

*Working Alliance Inventory* (WAI) [36] assesses working alliance between parents and their service providers. The current study employs the short-form, 12-item version of the WAI [37] and includes the components of goal, task, and bond. Goal is the extent to which the client and provider agree on goals of services. Task is the degree to which the client and provider agree on ways of achieving stated goals. Bond denotes mutual liking between client and provider.

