### Data collection points for outcome measures

Data collection for SC/SC+ fidelity will be conducted at each session of the intervention, throughout the course of service delivery. The CES-D is assessed at intake into SC, at the end of the intervention, and at the end of the study. The CTS-2, WAI, RSE, and relationship status measures are assessed at the beginning and conclusion of receiving the intervention (i.e., the HR curriculum, or the comparison time frame for the control condition). HR satisfaction is assessed at the conclusion of receiving the intervention, see Fig. 3 (SPIRIT figure for SafeCare+ trial for data collection timings).

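### Change is named as the dependent variable and the baseline score is not named as a covariate; baseline adjustment would give a more precise arm comparison from the same data

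*Protocol article*

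**What the plan says.** Under Quantitative analyses, the article chooses generalized linear mixed models because "measurements over time are nested within clients and clients are nested within provider". On the outcomes it says "Dependent variables will be changed in (1) reports of DV on the CTS, (2) depression, (3) relationship self-efficacy", and then adds fidelity as a fourth item. The first words are evidently a slip for change in. On covariates it says only that "The models tested involve both fixed and time-varying covariates"; the baseline value of the outcome is neither named nor ruled out.

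The schedule is under Data collection points for outcome measures:
- CTS2 and RSE, two occasions: "The CTS-2, WAI, RSE, and relationship status measures are assessed at the beginning and conclusion of receiving the intervention". The article explains this as the HR curriculum or the matching period in the control arm.
- CES-D, three occasions: "The CES-D is assessed at intake into SC, at the end of the intervention, and at the end of the study".
- Fidelity, during delivery only: "Data collection for SC/SC+ fidelity will be conducted at each session of the intervention, throughout the course of service delivery".

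Under Outcome measures, the CTS2 recall period differs between occasions. First, "Participants are asked about the frequency of concrete acts and events within the past 6 months for their baseline CTS2 assessment"; then, "with the time frame changed to assessing if these acts and events occur within the past 2 months for the post-intervention assessment".

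**The concern.** Subtracting the baseline gives it a fixed weight of one. Unless baseline and follow-up are perfectly correlated, that weight is too large when the SDs are equal, and surplus baseline noise enters the arm comparison. An arm-by-time term on raw scores with two occasions and free baseline means gives the same contrast in complete data, so it carries the same loss. Regression on baseline lets the data choose the weight.

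For CTS2 there is a further difficulty. A parent whose rate of acts never changed would report over a baseline window 6/2 = 3 times as long as the follow-up window. The raw difference is then hard to interpret as change, and the longer window may make the baseline more variable. A baseline covariate does not need the same scale as the outcome.

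At stake is the precision of the estimates from a pilot that is meant to inform the decision on a definitive trial.

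**Working it through.** **Inputs from the article.** At least 160 parents, 80 per arm (Design; Sample size); a medium Cohen's d (Sample size; Feasibility outcomes); the measurement times and recall windows given above.

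**Assumptions, since the article gives no figures.** d = 0.5 on the follow-up SD; two-sided alpha 0.05; equal baseline and follow-up SDs unless stated; linear model; one follow-up occasion; no provider clustering; r shown from 0.3 to 0.9.

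**The plan's own figure.** The 160 cannot be reproduced without alpha, power and dropout. At d = 0.5, a comparison of follow-up scores alone needs 126 parents for 80% power, 144 for 85% and 170 for 90%. With 80 per arm its power is 88.5%, so the description of 160 as adequate is plausible.

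**Variance per client of the arm contrast, in units of the follow-up variance.**
- Follow-up only: 1
- Change score: 2(1 − r)
- Baseline-adjusted: 1 − r²
- Ratio of adjusted to change: (1 − r²) / [2(1 − r)] = (1 + r)/2, below 1 for every r < 1

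**Power at 80 per arm**, as Φ(0.5 × √(80/2) / √variance − 1.96). Example at r = 0.3:
- Change: variance 1.4; 0.5 × 6.325 / 1.183 = 2.673; Φ(0.713) = 76.2%
- Adjusted: variance 0.91; 0.5 × 6.325 / 0.954 = 3.315; Φ(1.355) = 91.2%

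| r | Ratio (1+r)/2 | Power, change | Power, adjusted | n per arm for 80%, change | n per arm for 80%, adjusted |
|---|---|---|---|---|---|
| 0.3 | 0.65 | 76.2% | 91.2% | 88 | 58 |
| 0.5 | 0.75 | 88.5% | 95.5% | 63 | 48 |
| 0.7 | 0.85 | 98.3% | 99.3% | 38 | 33 |
| 0.9 | 0.95 | about 100% | about 100% | 13 | 12 |

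Below r = 0.5 the change score does worse than ignoring baseline altogether: 76.2% against 88.5% at r = 0.3.

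**Simulation check** (80 per arm, 4,000 replicates): variance ratios of 0.646, 0.744 and 0.878 at r = 0.3, 0.5 and 0.7, against 0.65, 0.75 and 0.85 from the formula. Both methods recovered the true difference of 0.5 on average (0.497 to 0.504), so neither is biased.

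**CTS2 with unequal SDs.** If the baseline SD is k times the follow-up SD, the change-score variance is 1 + k² − 2rk = (1 − r²) + (k − r)². The excess over the adjusted variance is (k − r)², which is never negative. With k = 1.5 (an illustration; the article gives no SDs) and r = 0.5, the variance is 0.75 + 1.00 = 1.75 and power is 66.7%, against 95.5% adjusted.

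**Levels of the model.** CTS2 and RSE have one follow-up value each, so a baseline-adjusted model has two levels, client within provider. CES-D has two follow-up values and keeps three.

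**The case against.** **A reader might infer that the plan contradicts itself.** Two occasions yield one change score per client, which leaves no occasion level for a three-level model. That follows only if the words mean a computed difference. The phrase is garbled, and it also governs fidelity, which has no pre-intervention value to subtract. Change over time on raw repeated scores is a fair reading, and it removes the conflict. Even on the literal reading, CES-D gives two changes per client. The text supports a request to clarify, not a claim that the model cannot be fitted.

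**A reader might infer that the loss occurs on any reading.** It does not. The unnamed fixed covariates could include baseline, and in a linear model a change score adjusted for baseline gives the same arm estimate as the adjusted follow-up score. A repeated-measures model with a common baseline mean would also avoid the loss. The article names neither and excludes neither.

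**The size depends on definitions.** If d is expressed in SDs of change, change-score power is 88.5% whatever r is, and the 76% does not arise. The ratio (1+r)/2 still holds: at r = 0.3 the adjusted analysis then has 0.5/√0.65 = 0.620 and Φ(0.620 × 6.325 − 1.96) = about 97.5%. At high r the gain is small. For a CTS2 frequency modelled with a non-linear link, the ratio need not hold.

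**The baseline may not precede allocation.** CTS2 and RSE are first measured at the start of the HR curriculum or comparison period, and the Discussion says that some parents assigned to SC+ may receive none of it. The order of allocation and measurement is not stated. This objection stands as a condition on the fix.

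**A reader might infer bias from chance imbalance and regression to the mean.** Over repeated randomisation that is the same imprecision seen in a single sample, not a separate bias.

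**Conclusion.** The point holds as one of efficiency and clear specification. The outcome is stated as change, baseline adjustment is not named, and on the two natural readings (change score, or arm-by-time with free baselines on two occasions) the analysis is less precise than it could be for any r < 1. Adjustment saves 35% of the variance at r = 0.3, 25% at 0.5, 15% at 0.7 and 5% at 0.9. The gain in power is material at low r and negligible at high r, under the assumptions listed in the working. The unequal CTS2 recall windows are a further reason not to use a raw difference for that outcome.

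The documents do not show bias in the randomised comparison, a model that cannot be estimated, or a trial that is too small.

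**What to change.** Reword the dependent-variable sentence in Quantitative analyses, and carry the same wording into the SAP:
- **CTS2 and RSE:** follow-up score as outcome, baseline score as covariate, arm as fixed effect, provider as random effect (two levels). Use a count-type link for CTS2 if its distribution calls for one.
- **CES-D:** the two follow-up scores as outcomes, with visit, arm-by-visit, baseline covariate, and client and provider random effects; or a repeated-measures model with a common baseline mean across arms.
- **Fidelity:** leave out of this change, as it has no pre-intervention value.
- **Timing:** confirm that the CTS2 and RSE baselines are taken before the arms' treatment diverges. If they are not, the case for adjusting on them, or for assuming a common baseline mean, must be made separately.

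The cost is wording and one check of timing. No new data or visits are needed.

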#### Sample size

A conservative estimate for the duration of the proposed study is 160 parents, which provides an adequate sample size required to discern improvement, with a medium Cohen’s *d* effect size, on the proposed measures.

## Discussion

This pilot study targets families with co-occurring DV and child maltreatment and will demonstrate the impacts of an early intervention approach for Latinx parents with histories of DV. The study addresses the needs of this target population by providing SC, an EB home visiting program designed for families reported for, or at risk of, child maltreatment, supplemented through the addition of an HR curriculum that has been modified specifically for Latinx families (SC+). This study design is appropriate for the target population because it provides a culturally and linguistically refined approach that promotes the development of individual skills such as problem solving, active decision-making, conflict resolution, and healthy communication—both for enhanced parenting and within personal relationships. The HR module is intended to help parents learn about the characteristics of healthy and unhealthy relationships so they may begin to examine and improve the quality of their own relationships. It is anticipated that as parents become active agents in creating and maintaining healthy personal relationships, they will provide a safer and more emotionally healthy environment for their children and will enhance their parenting effectiveness. Thus, the goals are to improve family stability by reducing conflict, improve communication in all areas of the parents’ life, and provide positive modeling for children. All services will promote integrity and self-sufficiency, improve access to resources, and increase the safety of adult and child survivors of DV and child maltreatment.

A primary aim of the RCT, pilot study is to demonstrate the effectiveness of the HR curriculum. A significant advantage of the design of the pilot study is the embedded nature of the RCT into a larger study. Substantial infrastructure support with regard to recruitment and data collection serve as an important foundation to success. A primary challenge of the RCT pilot study is that the inclusion of the HR curriculum into the existing service delivery system extends the length of services by 30% (~ 2 months). As a result, parents assigned to the intervention condition may not actually receive the entirety, or in some cases any, of the intervention due to the service requiring more time than the CWS timeline for length of service delivery. A study limitation is that parents with literacy challenges may have difficulty completing the outcome measures to determine effectiveness. In addition, the cultural appropriateness of outcome measures is a primary consideration. The first phase of the study is intended specifically to collaborate with technical assistance providers, community partners, and Latinx parents to ensure that the data collection efforts are aligned with the trauma-informed approach of the study.

Results from this study will inform the ways in which the CWS system of care may be strengthened to sustain long-term safety and well-being of children, while also providing efficacy data for a large, system-wide randomized control trial of the intervention. In addition, service providers are gaining multiple experiences with the provision of trauma-informed practice and intentional approaches to working with children and families with histories of DV. This pilot study provides an important foundational step to determining how DV services may be integrated into CWS home visitation programs, setting a platform for continued work with this population.

## Data Availability

The datasets generated during and/or analyzed during the current study are not publicly available due to ongoing recruitment and the sensitive nature of the study population, but are available from the corresponding author on reasonable request.

## Abbreviations

CBO: Community-based organization
CWS: Child welfare services
DV: Domestic violence
HR: Healthy relationships
RCT: Randomized control trial
SC: SafeCare
SC+: SafeCare with Healthy Relationships
